# Whole-body vibration training on functional capacity, vascular function, and glycemic control in individuals with type 2 diabetes and peripheral arterial disease: protocol for a randomized controlled trial

**DOI:** 10.3389/fendo.2026.1734560

**Published:** 2026-02-26

**Keywords:** blood flow, functional capacity (FC), peripheral arterial disease (PAD), RCT, type 2 diabetes, vibration

## Abstract

**Background:**

Type 2 diabetes and peripheral arterial disease contribute to long-term disability. Walking-based exercise improves related symptoms, but adherence is limited by low fitness and leg pain. Whole-body vibration stimulates muscle contractions and increases limb and microvascular blood flow, which can mimic the impact of walking. Prior studies suggest improved endothelial function, reduced arterial stiffness, and lower glycated hemoglobin following vibration therapy; however, its effects on functional capacity in this group remain unclear.

**Aims:**

To investigate whether whole-body vibration impacts functional capacity achieved with supervised treadmill walking, as measured by incremental shuttle walk test distance with a pre-specified non-inferiority margin.

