Whole-body vibration therapy (WBV) is a relatively new therapeutic modality. It involves the use of a mechanically oscillating platform to deliver low- to high-frequency vibrations throughout the body inducing involuntary muscle contractions (13), stimulating limb and microvascular blood flow. A meta-analysis showed increased peripheral blood flow following acute bouts of WBV in healthy subjects (14). However, to our knowledge, no studies have investigated the therapeutic effects of WBV on limb and microvascular blood flow and glycemic control in individuals with both T2D and PAD. WBV-induced muscle contractions can enhance venous return and shear stress, which are recognized systemic hemodynamic stimuli. These physiological responses underpin potential systemic and local vascular effects (15, 16). Evidence suggests that WBV can reduce arterial stiffness in young women with obesity (17) and improve endothelial function response in elderly with cardiovascular disease (18). Furthermore, a reduction in hemoglobin A1C, a marker for long-term glycemic control, has been reported following WBV training in individuals with T2D (19).

Importantly, improvements in vascular function and glycemic control are not merely surrogate markers but have the potential to translate into enhanced functional capacity. Functional capacity is a clinically meaningful endpoint in individuals with PAD, as it reflects mobility, independence, and quality of life in this population. Despite these potential links, it remains unclear whether WBV improves functional capacity as a downstream effect of enhanced vascular function and potentially improved glycemic control in individuals with T2D and PAD. Therefore, the objectives of this study are (i) to examine the effects of WBV on functional capacity in individuals with T2D and PAD, (ii) to determine the effects of WBV on vascular function, glycemic control, and quality of life in this population.

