The control group will attend supervised treadmill walking three times weekly for 12 weeks. The program will progressively increase in duration across the intervention period and will include stretching prior to and after each session. Walking speed and grade will be individually adjusted to reach the target intensity: participants with symptomatic PAD will walk until experiencing moderate claudication pain before resting and resuming, while those with asymptomatic PAD will walk continuously at a moderate intensity. In brief, both moderate intensities are assessed using subjective participant-reported measures. The moderate claudication pain in participants with symptomatic PAD is determined using a PAD-specific leg pain scale (26), a subjective pain intensity assessment tool. For individuals with asymptomatic PAD, moderate intensity is measured using the Borg Rating of Perceived Exertion (RPE) 6–20 scale (12, 13), a subjective exertion-based intensity measure, corresponding to moderate intensity as defined by the American College of Sports Medicine (ACSM) (27). The protocol was adapted according to Cochrane recommendations for standard walking therapy in PAD (11) (**Table 2**).

**Table 2 T2:** The 12-week treadmill walking training protocol.

Exercise components			Week					
			1–2	3–4	5–6	7–8	9–10	11–12
Warm-up			5–minute stretching					
Walking	Frequency (sessions/week)		3					
	Time (min)		15	20	23	25	27	30
	Intensity	Symptomatic PAD	• Start at 2.5–3.0 km/h, 0% grade • Adjusting speed (0.2–0.5 km/h) or grade (1–2%) to elicit a moderate claudication pain (3–4/5 claudication scale) within 3–10 min					
		Asymptomatic PAD	• Start at 2.5–3.0 km/h, 0% grade • Adjusting speed (0.2–0.5 km/h) or grade (1–2%) to maintain a moderate intensity (RPE 11–13)					
Cool-down			5–minute stretching					

PAD, peripheral arterial disease; RPE, rating of perceived exertion (Borg scale).

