### Primary outcome

The effectiveness of WBV will be assessed using the incremental shuttle walk test (ISWT) to examine changes in functional capacity (28). ISWT consists of 12 levels, with a total time signal of 12 minutes. Briefly, participants will be asked to walk on a 10-m long flat walkway following a beeping sound. The walking speed increased by 0.17 meters per second at one-minute intervals, beginning at 0.5 meters per second (level 1) and progressing to a maximum speed of 2.37 meters per second (level 12). The test will be terminated when participants cannot maintain the determined speed or meet the termination criteria following the exercise testing guidelines (29). The primary outcome will be the total distance covered during the test.

It should be noted that if a statistically significant beneficial intervention effect is observed, all patients in the control group will be offered the opportunity to undergo WBV.

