### Sample size calculation

The sample size was determined based on the primary outcome variable, maximum walking distance (MWD), as reported in a previous study by Zwierska et al. (37), which compared MWD between a leg exercise training group and a control (no exercise) group. Conservatively assuming a between-group difference of 50% of that reported by Zwierska et al., adjusting for baseline MWD, and using a two-sided α = 0.05 with 80% power, the required sample size was estimated at 25 participants per group. To account for a potential attrition of 15%, we aim to recruit 60 participants (30 per group). Sample size calculation was performed using the G*Power program (38).

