### Data reporting and statistical analyses

Demographic and clinical characteristics of participants at baseline will be reported for each group. The effectiveness of WBV on the primary outcome (ISWT) will be assessed on the intention-to-treat principle using all data collected on randomized participants. Data will be analyzed using a general linear model, adjusted for the participant’s age, sex, PAD categories (symptomatic or asymptomatic), diabetes duration, and the distance covered in the ISWT at baseline. The effect size will be reported as the adjusted between-group difference and its 95% confidence interval (CI). The potential interactions between randomization group and sex will be tested, and sex-specific differences reported as appropriate.

The same model structure will be used to examine the potential effectiveness of the intervention on secondary outcomes. Per-protocol analyses may be also carried out on primary and secondary outcomes excluding recipients with major protocol violations, in particular, lower levels of adherence (defined as completion of <67% of prescribed sessions).

Data will be analyzed using SAS v9.4 (SAS Institute, Cary, NC, USA) and/or SPSS v31 (IBM Corp, Armonk, NY, USA). Missing data on the primary outcome will not be imputed. All statistical tests will be two-sided at p<0.05, with no adjustment for multiple comparisons (44). Trial findings will be reported according to CONSORT 2010 guidelines (45).

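### The abstract announces non-inferiority to treadmill walking, but the objectives, sample size, tests and post-trial rule all plan for a two-sided difference, and no margin is given

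*Protocol article*

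**What the plan says.** The Aims in the abstract set WBV against supervised treadmill walking on incremental shuttle walk test (ISWT) distance: "as measured by incremental shuttle walk test distance with a pre-specified non-inferiority margin". This is the only mention of non-inferiority or of a margin in the article.

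The other sections read differently:

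- **Introduction, objectives:** the first objective is "to examine the effects of WBV on functional capacity in individuals with T2D and PAD".
- **Study design:** the comparator is active. "The control group will attend supervised treadmill walking three times weekly for 12 weeks".
- **Primary outcome:** "if a statistically significant beneficial intervention effect is observed, all patients in the control group will be offered the opportunity to undergo WBV".
- **Sample size calculation:** 25 per group for a between-group difference at two-sided α = 0.05 and 80% power. The difference is half of that in an earlier study "which compared MWD between a leg exercise training group and a control (no exercise) group".
- **Data reporting and statistical analyses:** the adjusted between-group difference is reported with its 95% confidence interval, by intention to treat. "All statistical tests will be two-sided at p<0.05, with no adjustment for multiple comparisons". "Per-protocol analyses may be also carried out on primary and secondary outcomes".

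**The concern.** Non-inferiority and difference testing have different null hypotheses, success criteria and sample sizes. A reader of the abstract expects a conclusion that WBV is, or is not, acceptably close to walking. A reader of the body expects a test of whether the arms differ.

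The conflict matters most if the result is non-significant. WBV is proposed because adherence to walking is poor, so a finding of no significant difference from walking could easily be taken as success, and the abstract's wording encourages that. The article gives no fixed criterion against which to check such a claim. Participants and assessors are unblinded, so a margin first made public alongside the results would carry little weight.

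**Working it through.** **1. The plan's own figure.** Inputs from the Sample size calculation: 25 per group, 15% attrition. 25 / (1 − 0.15) = 29.4, rounded up to 30 per group, 60 in total. This reproduces. The 25 itself cannot be reproduced, because neither the difference in metres nor the SD is stated. (The abstract gives 48 participants; that is a separate discrepancy, and 25 per group is used below.)

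**2. Implied planning difference.** Solve a two-sample t-test for the standardized difference d with n = 25 per group, two-sided α = 0.05 and power 80%. The result is d = 0.809 residual SD. The normal approximation gives (1.960 + 0.842) × √(2/25) = 0.79.

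**3. Width of the planned interval.** Half-width = t(0.975; 48 df) × √(2/25) = 2.011 × 0.2828 = 0.569 SD.

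**4. What a non-significant result would mean.** If WBV is truly worse by half the planning difference (0.809 / 2 = 0.404 SD), the noncentrality is 0.404 × √(25/2) = 1.43. The power to detect the deficit is 0.288, so p>0.05 occurs with probability 1 − 0.288 = 0.71. At a true deficit of 0.5 SD the probability is 0.59. A non-significant test is thus the likelier outcome even when WBV is worse by a sizeable amount.

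**5. Non-inferiority power at the planned size.** The article gives no margin, so margins here are assumptions in residual SD units. The true difference is taken as 0, and the criterion is that the lower limit of the two-sided 95% interval lies above minus the margin (one-sided 0.025). Power is the probability that a noncentral t with 48 df and noncentrality margin × √(25/2) exceeds 2.011.

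| Margin (SD) | Power, t | Power, normal approximation |
|---|---|---|
| 0.8 | 79% | 81% |
| 0.6 | 55% | 56% |
| 0.5 | 41% | 42% |
| 0.4 | 28% | 29% |

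Power of 80% at 25 per group needs a margin of about 0.81 SD by the t calculation (0.79 by the normal), which is the whole planning difference from step 2.

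**6. Size needed for a smaller margin.** By the normal approximation, n per group = 2 × ((1.960 + 0.842) / margin)². For 0.5 SD this is 62.8, so 63; for 0.4 SD it is 98.1, so 99. Exact t calculations add one in each case (64 and 100). At 15% attrition, recruitment per group would be 63 / 0.85 = 74.1, so 75, and 99 / 0.85 = 116.5, so 117.

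These calculations ignore the few degrees of freedom used by the covariates. They are in units of the residual SD after adjustment, and the article does not say how far adjustment reduces the raw SD.

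**The case against.** The strongest defence is that the non-inferiority clause is one stray phrase in an abstract, and that everything operative describes a difference. That may well be the right diagnosis. It leaves the contradiction standing but makes deletion of the phrase a full remedy, so the review should not assume that non-inferiority is the true aim.

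Three stronger readings are tempting, and the document does not support them.

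- **That the non-inferiority question cannot be answered by this design.** The planned adjusted difference and 95% interval can carry a non-inferiority decision without any change of model. What the article lacks is the margin, the rule and a sample size tied to them.
- **That no margin was ever fixed, or that one will be picked after the data.** The article says it is pre-specified, and an unseen full protocol or analysis plan may hold it. The article also nowhere says that p>0.05 will be read as equivalence. Yet a margin held elsewhere would not reconcile a sample size built for a difference, or a post-trial rule that depends on significant benefit, with a non-inferiority aim.
- **That the optional per-protocol analysis is a defect in itself, or that crossover will dilute the comparison.** Per-protocol support matters only if non-inferiority is kept. Requiring it to confirm intention to treat is one convention, and excluding low adherers after randomization can introduce its own bias. The document gives no basis for expecting crossover during the trial.

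It is also fair to say that the SD-unit margins are illustrative. The planning difference comes from exercise against no exercise and is not a natural yardstick for a margin against an active comparator.

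**Conclusion.** The point holds as an internal contradiction on the primary hypothesis, and it should be settled before data are seen. The abstract promises non-inferiority with a margin; the objectives, post-trial rule, sample size and tests describe a two-sided difference. Followed as written, the plan cannot turn a non-significant result into a claim of non-inferiority: the interval half-width is about 0.57 residual SD, and a true deficit of 0.40 SD would be missed about 71% of the time.

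If non-inferiority is the real aim, the planned size is adequate only for a margin of about 0.8 SD. These sizes assume 25 evaluable per group, a two-sample t comparison, and, for non-inferiority power, a true difference of zero. The contradiction itself rests on the text alone and on none of these assumptions.

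**What to change.** Choose one hypothesis and align the abstract's Aims, the objectives in the Introduction, Primary outcome, Sample size calculation, and Data reporting and statistical analyses.

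**(a) If a difference is intended:** delete the non-inferiority wording from the Aims, and state in the analysis section that p>0.05 will not be read as equivalence or non-inferiority.

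**(b) If non-inferiority is intended:**

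- State and justify the margin in metres of ISWT distance before any data are seen.
- Declare non-inferiority only if the lower limit of the already planned two-sided 95% interval for the adjusted WBV-minus-walking difference lies above minus the margin. Test superiority afterwards.
- Make the per-protocol analysis of the primary outcome a planned supportive analysis.
- Restate power for that margin at the planned size.
- Reconcile the sentence on offering WBV to the control group with the hypothesis kept.

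**Cost.** Option (a) costs wording only. Option (b) costs wording and one comparison of a planned interval with a fixed number, plus a less favourable stated power if the margin is below about 0.8 SD. Restoring 80% power would then need more participants: about 63 evaluable per group for 0.5 SD and 99 for 0.4 SD by the normal approximation.

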**Study design:**

Randomized controlled trial of 48 participants (24 per group) aged 50 years or older with ankle-brachial index 0.9 or less or toe-brachial index 0.7 or less and Fontaine stage I to IIb will be included. Participants will receive whole-body vibration or supervised treadmill walking for 12 weeks, three sessions per week. Whole-body vibration will be delivered using a Galileo plate. Analyses will follow the intention-to-treat principle using a general linear model adjusted for age, sex, peripheral arterial disease category, diabetes duration, and baseline incremental shuttle walk test distance.

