### Study design

This will be a randomized controlled trial, with participants randomized in a 1:1 ratio to either walking (control arm) or whole-body vibration (WBV; treatment arm) (**Figure 1**) using a computer-generated randomization sequence with variable block sizes of 2 and 4 (23). Randomization will be stratified by biological sex (male, female), ensuring that within each sex stratum the group allocation is balanced.

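### The abstract gives a trial of 48 (24 per group), but the sample size section needs 25 per group before attrition and recruits 60; 48 with the planned attrition gives about 71% power, not 80%

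*Protocol article*

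**What the plan says.** The abstract, under Study design, presents a "Randomized controlled trial of 48 participants (24 per group" as the size of the trial. It does not describe 48 as a number of completers.

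The Sample size calculation section gives different figures. At a two-sided 5% level with 80% power and adjustment for baseline walking distance, "the required sample size was estimated at 25 participants per group". It then inflates for dropout: "To account for a potential attrition of 15%, we aim to recruit 60 participants (30 per group".

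Two other statements bear on the point. Allocation is 1:1 (Study design in the methods), so per-group and total figures convert directly. Under Data reporting and statistical analyses, "Missing data on the primary outcome will not be imputed", so a participant without a follow-up walk test does not contribute to the primary analysis.

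**The concern.** Both figures are stated as the current plan, and each agrees with its own per-group number (2 × 24 = 48; 2 × 30 = 60), so neither looks like a single mistyped digit. The abstract's figure is below the recruitment target and also below the 50 evaluable participants that the calculation requires before any allowance for dropout.

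The sample size fixes when recruitment ends. If it ends at 48, the trial falls short of the power it claims. A reader of the eventual report also could not tell whether a trial of 48 was complete or 12 short of target. The Blinding section says that participants cannot be blinded and that blinding those who oversee assessments would be difficult. With two targets in print, stopping at either could later be presented as planned. Nothing suggests that this is intended, but a single fixed target removes the possibility.

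**Working it through.** **Inputs.** From Sample size calculation: 25 per group required, two-sided α = 0.05, power 80%, attrition 15%, recruitment 60 (30 per group). From the abstract: 48 (24 per group).

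**Step 1: reproduce the recruitment target.** 25 / (1 − 0.15) = 29.4, rounded up to 30 per group, 60 in total. The sample size section is consistent with itself.

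**Step 2: test 48 against the same inputs.**
- As an evaluable number: 24 < 25, so it is short by one per group with no dropout.
- As a recruited number: 24 × 0.85 = 20.4 evaluable per group (48 × 0.85 = 40.8 in total), against 25 (50 in total).
- Room for dropout: 60 randomised can lose 1 − 50/60 = 16.7% and still reach 50. With 48 there is no room at all.

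**Step 3: anchor the effect size.** The 25 per group cannot be re-derived. The section says only "Conservatively assuming a between-group difference of 50% of that reported by" a cited study and gives no difference, SD or correlation. The assumption made here is therefore that 25 per group gives exactly 80% power. With d the between-group difference in units of the residual (baseline-adjusted) SD:
- Normal approximation: power = Φ(d√(n/2) − 1.96). Setting n = 25 and power = 0.80 gives d = 0.792.
- Two-sample t: df = 2n − 2, noncentrality d√(n/2). Setting n = 25 and power = 0.80 gives d = 0.809. Removing one further degree of freedom for the covariate leaves d at 0.809.

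Because a required n is rounded up, the true d could be slightly larger. The upper limit is the d at which 24 per group already gives 80% (d = 0.809 normal, 0.826 t).

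**Step 4: power at each number.** Worked example, normal approximation at n = 20.4: 0.792 × √10.2 − 1.96 = 0.57, and Φ(0.57) = 0.716.

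| Scenario | Evaluable per group | Normal, d = 0.792 | t, d = 0.809 | Upper limit, t, d = 0.826 |
|---|---|---|---|---|
| 48 randomised, no attrition | 24 | 78.4% | 78.3% | 80.0% |
| 48 randomised, 15% attrition | 20.4 | 71.6% | 71.2% | 73.0% |
| Stated requirement | 25 | 80.0% | 80.0% | 81.7% |
| 60 randomised, 15% attrition | 25.5 | 80.8% | 80.8% | 82.4% |

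With whole numbers in place of 20.4, the t result at d = 0.809 is 70.3% for 20 per group and 72.5% for 21.

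**The case against.** The strongest reply is that the power loss depends on how 48 is read. If it meant evaluable participants, power would be between 78.3% and 80.0%, a loss of under two points that nobody would act on. That is correct, and the material loss does come from attrition. But the abstract gives 48 as the size of the trial, the 15% attrition is the protocol's own figure, and missing primary outcomes are not imputed. Even on the evaluable reading, 24 is not the 25 that the calculation gives.

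A second reply is that the power figures rest on a back-solved effect. This also stands: they are conditional on the stated 25 per group and should be read as a range. The contradiction between 48 and 60, and the fact that 24 is below 25, need no such assumption.

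Third, the effect behind the 25 comes from exercise against no exercise, whereas this trial compares vibration with supervised walking, so the 80% may not describe this trial even at 60. That is a separate weakness of the calculation. It does not explain the two sample sizes.

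Finally, 48 could be the remnant of another calculation: 20 per group with 15% attrition gives 20/0.85 = 23.5, rounded up to 24. The article says nothing of the kind. If that is the origin, that calculation should be shown.

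**Conclusion.** The concern holds. The article states two incompatible sample sizes, and the one in the abstract does not meet the article's own requirement under any reading. Only 60 follows from the stated inputs. If 48 are randomised and 15% are lost, power is about 71%, and at most about 73%, against the stated 80%: a shortfall of about 7 to 9 percentage points. With no losses the shortfall is at most about 2 points. These power figures assume that 25 per group gives 80% power, which cannot be verified from the article, and that losses are equal in the two groups.

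**What to change.** Change the abstract to 60 participants (30 per group), and make the same change in the registry entry if it carries 48 (that entry was not available to check). The cost is one line. Because 60 is already the target in the methods, no patients are added.

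If 48 is the real target, correct the sample size section instead: give 48 as the number to be randomised and state the power as about 71% after 15% attrition under the same assumptions, or show the separate calculation from which 48 came. The cost is then a lower stated power. Either way, one target should appear throughout and be fixed before outcome data are examined.
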